### Participant timeline {13}

Participants are followed from the time of enrolment through until study close-out, 1 week following their final assessment visit. The schedule of enrolment, randomisation, interventions, and assessments is shown in Fig. 2.

**Fig. 2 Fig2:**
[figure not shown]
Participant timeline. Standard Protocol Items: Recommendations for Interventional Trials (SPIRIT) checklist. Enrolment, interventions, and assessments. GSRS, gastrointestinal symptom rating scale; EQ-5D, EuroQol five dimensions questionnaire; AE, adverse events; SAE, serious adverse events

### Sample size {14}

This study aims to enrol 120 patients across both sites, with 60 assigned to the sirolimus intervention group and 60 assigned to control. This will provide 80% statistical power (alpha 0.05) to detect an absolute difference of 25% in the proportion of patients who achieve the serological neutralisation titre threshold necessary to provide clinical protection from COVID-19 disease, allowing for a 10% drop-out rate.

### Recruitment {15}

Prospective participants will be identified through the following means:Review of local transplant recipient databases at each trial site. (Only local site clinical staff will have access to identifying information for the purpose of recruitment.)During routine clinical review with their treating nephrologist or transplant centre.Potential participants may have also indicated their interest in trial participation by responding to a QR code displayed during the Transplant Australia COVID Vaccination Update Webinar, broadcast in November 2021.

Potential participants will be approached by their treating nephrologist and offered the opportunity to participate in the trial. Prior to enrolling, patients will be provided with written information regarding the rationale behind the trial, the potential risk and benefits of participation, and the personal commitment involved. Recruitment will continue until target recruitment is fulfilled, or until recruitment of dual-vaccinated transplant recipients is no longer feasible, or if delaying a third vaccination becomes no longer ethically permissible due to clinical urgency. Participants will not receive payment for participation.

## Assignment of interventions: allocation

### Sequence generation {16a}

Participants will be randomised 1:1 to either sirolimus (intervention) or mycophenolate (control). Randomisation will occur via computer-generated stratified block randomisation with randomly permuted block sizes of 2, 4, and 6. Stratification will occur by site and the response to a two dose COVID-19 vaccine schedule (low responder anti-RBD IgG 0.4 - 99 U/mL; or non-responder, anti-RBD IgG < 0.4 U/mL).

### Concealment mechanism {16b}

The allocation sequence is contained and administered centrally through an external web-based randomisation module contained within a purpose-built Research Electronic Data Capture (REDCap) data management platform. The randomisation algorithm and treatment allocation are not accessible to study investigators or research staff.

### Implementation {16c}

The allocation sequence will be generated by an independent and blinded statistician. Trained study investigators will enrol participants, at each study site, and will perform randomisation via the web-based platform and assign the intervention to each participant.

## Assignment of interventions: blinding

### Who will be blinded {17a}

Given the significant changes in prescribed immunosuppression, neither the study participants nor clinical staff will be blinded to treatment allocation. Scientific staff performing the laboratory assays for primary and secondary outcomes will be blinded to patient treatment allocation.

### If blinded, circumstances under which unblinding is permissible, and procedure for revealing a participant’s allocated intervention during the trial {17b}

The design is open label with only outcome assessors being blinded so unblinding will not occur.

## Data collection and management

### Plans for assessment and collection of outcomes {18a}

Trial data are collected prospectively by trial staff and entered on to web-based electronic case record forms (eCRF) maintained on a bespoke REDCap database.

Clinical and laboratory data are collected by study staff from the participant’s electronic medical record. Safety laboratory tests (haematology, chemistry, urinalysis) and enrolment criteria (anti-RBD IgG) are performed at the hospital laboratory of each study site. Blood samples for immunological assessment will be collected by clinical research staff and processed in the on-site immunology laboratory at the Royal Adelaide Hospital. Estimation of participants’ habitual diet will be captured using a 4-day food diary, completed at the time stool samples are collected. Validated questionnaires are completed by participants to capture health-related quality of life (EQ-5D) information.

### Plans to promote participant retention and complete follow-up {18b}

Participants who withdraw from the study, are lost to follow-up, or permanently discontinue the study intervention will be asked to continue with scheduled study visits and follow-up. Outcome data relevant to the trial will be collected from clinical records unless the participants specifically withdraws consent. Reasons for withdrawal, discontinuation, or deviations from the study protocol will be captured in an eCRF.

### Data management {19}

All study data are collected by trained research staff and entered directly onto study-specific electronic data capture forms created and housed within a secure, web-based data management tool (REDCap). The data capture forms contain inbuilt protections to promote data quality, including range checks for numerical data values, restrictions on alphanumeric entries, and prevention of duplicate records. The RIVASTIM REDCap database is stored on secure servers in an on-site limited access data centre at the Royal Prince Alfred Hospital and operated behind the Sydney Local Health District (SLHD) firewall. All electronic information and transmissions are protected via Secure Sockets Layer (SSL) encryption. Access to the RIVASTIM REDCap database is limited to approved research staff, with individual user authentication and logging of all data entry and modification, and access to restricted modules (randomisation, scheduling, and data export) privileged. The database in maintained by the SHLD Information and Communication Technology (ICT) Services with regular back-up processes in place.

### Confidentiality {27}

Prior to study enrolment, participants will consent to research staff accessing their electronic medical record to obtain baseline and demographic information, and the results of laboratory assessments. The privacy and confidentiality of screened and enrolled participants will be preserved with all study data stored in the RIVASTIM REDCap database under a unique numerical study identifier. Access to personal identifying information for participant contact and safety will be limited to trial research staff with privileged access to the REDCap database. Privacy mechanisms within the RIVASTIM REDCap database will remove potential identifiers from data exported for downstream analysis.

No identifying information or individually identifiable participant data will be reported in publications, presentations, or in any report arising from this study.

### Plans for collection, laboratory evaluation, and storage of biological specimens for genetic or molecular analysis in this trial/future use {33}

Blood samples will be taken from participants for immunological assessment at randomisation and at 4–6 weeks following vaccination. Blood will be drawn from participants by clinical research staff and collected in 7 × 9mL lithium heparin and 1 × 8mL CAT serum separator vacutainer tubes. Peripheral blood mononuclear cells (PBMCs) will be isolated from whole blood by density gradient centrifugation in Ficoll-Paque and aliquoted and cryopreserved in liquid nitrogen for batch testing. Sera will be aliquoted and stored at -80°C. Phenotypic and functional assessments of vaccine specific T and B-cell responses will be determined using a variety of laboratory techniques including but not limited to cytometric analysis with intracellular cytokine staining and activation-induced marker (AIM) assays and IFNγ enzyme-linked immunosorbent spot (ELISpot) assays. Using participant serum, the titres of SARS-CoV-2 spike-protein-specific IgG and the capacity of participant serum to neutralise SARS-CoV-2 viral entry into ACE2^+^ cells will be assessed. The capacity of pre- and post-immunisation serum to induce spike-protein-specific antibody-dependent innate immune responses will be measured.

Stool samples will be self-collected by participants using an at home collection kit (OMNIgene GUT OM-200, DNA Genotek, Canada) at baseline and at time of 3^rd^ vaccine dose. Stool samples will be aliquoted and stored at −80°C until batch testing. Analysis of the faecal metagenome will be performed by comparative sequencing of the 16S-rRNA amplicons (V3-V4 region) to identify changes in community structure, relative abundance, and functional characteristics of the gut microbiome.

All biological specimens will be deidentified and labelled with the participants unique study identifier. Stool and blood samples will be stored and maintained in access-restricted laboratory freezers at their corresponding trial site (Adelaide Health and Medical Sciences building, Adelaide, or the Transplant Institute, RPA, Sydney).

## Statistical methods

### Statistical methods for primary and secondary outcomes {20a}

The primary analysis will be by intention-to-treat, with participants assessed according to their treatment allocation. Participants who develop a positive SARS-CoV-2 PCR result during the study will be excluded from the primary analysis to avoid confounding. A per-protocol analysis will also be reported, with participants who failed to adhere or tolerate sirolimus, and participants who withdrew or were lost to follow-up excluded from the analysis. A sensitivity analyses adjusting for potential confounding may be performed should significant imbalances in baseline characteristics between the treatment groups occur.

The primary endpoint is the proportion of patients who achieved a post-intervention serological neutralisation of live SARS-CoV-2 virus (20.2% of the mean neutralisation level of a standardised cohort of COVID-19 convalescent individuals) in both groups using the chi-square test. An unadjusted and adjusted relative risk (RR) will be calculated. For the adjusted RR estimate, the primary outcome of a threshold SARS-CoV-2 serological neutralisation titre will be analysed using a log-binomial regression model. The initial immune response to a two-dose vaccine schedule (anti-RBD IgG titre; low responder: 0.4–99 U/mL; or non-responder: <0.4 U/mL) will be included in the model as a fixed effect, with study site as a random effect.

Secondary outcomes will be analysed using univariate and multivariate methods dependant on the outcome type. Baseline characteristics and demographic data will be reported as mean ± SD for normally distributed data and median ± IQR for non-normally distributed data, with categorical variables reported as frequencies. All statistical analyses will be described in detail with arising publications. A two-sided significance level of 5% will be used for all analyses.

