### Management of COVID-19-positive participants during the trial

Study participants who returned a positive COVID-19 result during the trial will be managed in consultation with their treating transplant unit as per local best practice. Participants who contract COVID-19 following randomisation but prior to a third vaccination may have their third vaccine dose delayed. Where possible, participants will be asked to continue with their allocated treatment regimens and attend study visits and follow-up. Positive COVID cases will be excluded from the primary analysis as SARS-CoV-2 infection will confound assessment of the primary outcome measure.

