### Outcomes {12}

#### Primary outcome measure

The primary outcome is the proportion of participants in each trial arm who develop protective serological neutralisation of live SARS-CoV-2 virus (ancestral strain) at 4–6 weeks following a third COVID-19 vaccination. The protective level is defined as 20.2% of the mean neutralisation level of a standardised cohort of COVID-19 convalescent individuals. This threshold correlates with 50% protection from infection with SARS-CoV-2 (ancestral strain) in the general population [31].

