#### Secondary outcome measures

The secondary outcome measures include the following:2.The proportion of participants in each trial that reach a threshold of serological anti-SARS-CoV-2 (ancestral strain) RBD IgG antibody ≥ 100 units/mL (measured with an Elecsys Anti-SARS-CoV-2 immunoassay [Roche], and equivalent to 100 BAU/mL). This RBD IgG threshold was chosen on the basis of pre-clinical and clinical studies and is consistent with the reported outcomes in published COVID-19 clinical vaccine trials [6].3.The development of COVID-19 following randomisation, determined by:Positive SARS-CoV-2 PCR test, or rapid antigen test in the setting of symptomatic diseaseDetection of SARS-CoV-2 anti-nucleocapsid antibodies at the time of primary outcome assessment.4.Change in the median magnitude of the SARS-CoV-2 spike-specific, antiviral T cell response prior to and at 4–6 weeks following vaccination, determined as the frequency of cells that secrete IFNγ in response to stimulation with spike-protein (ancestral strain)-derived peptides.5.Phenotypic and functional characterisation of T and B lymphocyte populations6.Tolerance of sirolimus as determined by drug cessation, drug adherence, and drug-related adverse events including proteinuria, anaemia, leukopenia, rash, mouth ulcers, and pneumonitis.7.Adverse events following immunisation (AEFI) including adverse events of special interest (AESI) will be assessed via phone consultation at 1 week, and again at 4–6 weeks post-vaccination during the final follow-up visit, and include:Changes in kidney allograft function, determined by serum creatinine, eGFR (CKD-EPI equation), and proteinuriaThe occurrence of biopsy proven acute allograft rejectionThe recurrence of primary kidney diseasePatient-reported quality of life as recorded by the EQ-5D questionnaire8.Changes in the community structure, relative abundance, and functional characteristics of the gut microbiome following 4 weeks of sirolimus intervention, determined by 16S-rRNA metagenomic sequencing of participant stool samples.

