### Methods for additional analyses (e.g. subgroup analyses) {20b}

Subgroup analyses will be performed to examine for statistical interaction between the treatment arm and (1) initial response to 2-dose vaccine schedule (non-responder or low-responder) and (2) duration between previous vaccine dose (less than, or greater than 6 weeks) and randomisation. Patients who develop primary COVID-19 infection during the study period will have both primary and secondary outcomes analysed as a pre-specified subgroup analysis.

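### Infection is defined differently for the primary-analysis exclusion, the secondary outcome and the infected subgroup, so it is unsettled who is in the primary analysis, which is also labelled intention-to-treat

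*Protocol article*

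**What the plan says.** Four places in the protocol article deal with infection after randomisation.

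- **Statistical methods {20a}**, on the primary analysis: "Participants who develop a positive SARS-CoV-2 PCR result during the study will be excluded from the primary analysis to avoid confounding". The sentence before it reads: "The primary analysis will be by intention-to-treat, with participants assessed according to their treatment allocation".
- **Management of COVID-19-positive participants**, on the same analysis: "Positive COVID cases will be excluded from the primary analysis as SARS-CoV-2 infection will confound assessment of the primary outcome measure". That section opens with "Study participants who returned a positive COVID-19 result during the trial" and names no test.
- **Secondary outcome measures, item 3**, defines COVID-19 after randomisation as a positive PCR, or a "rapid antigen test in the setting of symptomatic" disease, or detection of "SARS-CoV-2 anti-nucleocapsid antibodies at the time of primary outcome assessment".
- **Additional analyses {20b}**: "Patients who develop primary COVID-19 infection during the study period will have both primary and secondary outcomes analysed as a pre-specified subgroup analysis". Again no test is named.

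The endpoint is a threshold on live-virus neutralisation: "The protective level is defined as 20.2% of the mean neutralisation level of a standardised cohort of COVID-19 convalescent individuals".

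**The concern.** Both exclusion sentences give the same reason: infection confounds the neutralisation endpoint. That endpoint cannot tell antibody raised by infection from antibody raised by the third dose. The protocol accepts nucleocapsid antibody as evidence of infection, because it excludes on it at entry and measures it at the outcome visit. Yet {20a}, read literally, ignores it when forming the primary set, and ignores rapid antigen tests too.

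At stake is the membership of the primary analysis. Two analysts following two sections of the same document could analyse different people, and the choice could be made after results are seen. The trial status table gives rising community prevalence as a reason for early closure, so such cases are plausible.

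The second issue is the label. Dropping participants for an event after randomisation leaves a selected set, whichever definition is used. Participants and clinical staff know the allocation, and treatment may affect the event: the background section cites a 50% reduction in viral infections on an mTOR-inhibitor regimen in an earlier study.

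**Working it through.** **Step 1. The definitions side by side.** How each rule treats a participant with no positive PCR:

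| Only evidence of infection | {20a} | COVID-19 management section | Secondary outcome 3 | Subgroup {20b} |
|---|---|---|---|---|
| Rapid antigen, symptomatic | kept | excluded | infected | not stated |
| Rapid antigen, no symptoms | kept | excluded | not counted | not stated |
| Anti-nucleocapsid at outcome visit | kept | unclear (is this a positive COVID-19 result?) | infected | not stated |

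Every row contains a disagreement or a gap.

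**Step 2. The plan's own figure.** The sample size section gives 60 per arm, 80% power, a 25-point difference, two-sided 5% and 10% drop-out, so 60 × 0.9 = 54 evaluable per arm. No control rate is stated. The figure reproduces at 20% vs 45% (or 55% vs 80%): n = 54, 54/0.9 = 60, power 80.1%. This point does not dispute it.

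**Step 3. Effect of keeping infections that {20a} misses.** The documents give neither an infection rate nor a control response rate, so the following are assumptions: response 40% vs 65%; 54 per arm; a share f infected but not PCR-positive; a share c of the infected who would otherwise fail crossing the threshold; infection unrelated to vaccine response.

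Observed rate if kept: p + f·c·(1 − p). If excluded, the rate stays p and the arm shrinks to 54(1 − f).

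Power = Φ[(d − 1.96·SE₀)/SE₁], with SE₀ from the pooled rate and SE₁ from the separate rates.

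*f = 10% in both arms, c = 1.* Control 0.40 + 0.10 × 0.60 = 0.46; sirolimus 0.65 + 0.10 × 0.35 = 0.685; d = 0.225. SE₀ = √(2 × 0.5725 × 0.4275/54) = 0.0952; SE₁ = √((0.2484 + 0.2158)/54) = 0.0927. Power = Φ(0.414) = 66.1%. Excluding leaves 48.6 per arm at 40% vs 65%: 70.0%.

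*f = 10% control, 5% sirolimus, c = 1.* 0.46 vs 0.65 + 0.05 × 0.35 = 0.6675; d = 0.2075; power 58.7%. Excluding leaves 48.6 and 51.3: 71.2%.

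*f = 10% in both arms, c = 0.5.* 0.43 vs 0.6675; d = 0.2375; power 70.4%.

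| Scenario | Kept: difference, power | Excluded: difference, power |
|---|---|---|
| 10% / 10%, all cross | 22.5 points, 66% | 25 points, 70% |
| 10% / 5%, all cross | 20.75 points, 59% | 25 points, 71% |
| 10% / 10%, half cross | 23.75 points, 70% | 25 points, 70% |

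**Other response rates.** At 20% vs 45%, with 10% per arm and all crossing, keeping them gives 22.5 points and 67% power; excluding them gives 25 points and 76%.

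**Step 4. Direction when unbalanced.** Suppose no true effect, 25% in each arm, and retained infections of 5% in one arm and 15% in the other, all crossing. The rates become 0.25 + 0.05 × 0.75 = 28.75% and 0.25 + 0.15 × 0.75 = 36.25%. That is a spurious 7.5 points, with a rejection rate of about 13% instead of 5%, in favour of whichever arm holds more retained infections.

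**The case against.** The COVID-19 management section already excludes positive cases from the same analysis for the same reason. If it governs, a participant positive by rapid antigen is out. A reader might infer that infected sera will certainly count as vaccine successes. The documents do not support that: it requires {20a} to prevail and the serum to cross the threshold. The defect is an unresolved conflict with a possible bias. This part of the objection stands.

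A reader might also set 66% against the 75% power (74.6%) of a trial with no infections. That is the wrong comparator, because excluding infected participants also costs sample size. The relevant gap in the balanced case is about 4 points (66.1% vs 70.0%), and it disappears if only half cross. Full crossing is not assured in patients selected for poor antibody response and tested against the ancestral strain.

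It can also be said that {20b} does not announce a comparison of arms among the infected. That is correct. The interaction tests listed there concern response to two doses and the interval since the previous dose, so a descriptive reading of the infected subgroup fits the text. To say that the protocol plans an invalid comparison would go too far.

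Finally, the exclusion is disclosed directly after the intention-to-treat statement, the earlier viral-infection finding is not about SARS-CoV-2 in this short intervention, and an all-randomised sensitivity analysis may sit in an analysis plan not shown. The label is therefore the lesser part of the point. None of this reconciles the sections on who belongs in the primary analysis.

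**Conclusion.** The point holds as a conflict of definitions that determines the primary analysis set, with a secondary fault in calling that set intention-to-treat. Under {20a} as written, infections identified only by rapid antigen or anti-nucleocapsid remain and could count as responses. With balanced infections the difference shrinks; with unbalanced infections the bias can go either way, and the documents do not fix its direction.

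Under the stated assumptions the dilution runs from 1.25 to 4.25 points of a 25-point difference, and the power cost relative to exclusion from nil to about 12.5 points. These are illustrations, since the infection, response and crossing rates are all assumed. The excluded figures keep 25 points only if infection is unrelated to vaccine response. Recruitment closed before 120, so the actual arms are smaller than 54 would suggest and each misclassified participant weighs more.

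**What to change.** 1. Use one infection definition for the primary-analysis exclusion, secondary outcome 3 and the infected subgroup: the one in secondary outcome 3, including anti-nucleocapsid at the outcome sample, covering randomisation to that sample. State explicitly how a positive rapid antigen test without symptoms is handled, because the management section and secondary outcome 3 differ on it.
2. Describe the resulting population as the infection-free set, not as intention-to-treat.
3. Beside it, report the analysis of all randomised participants with an outcome sample regardless of infection, and tabulate exclusions by arm and by type of test. This matters more once the exclusion is widened, because a wider exclusion on a post-randomisation event is still a selection.
4. State that results in the infected subgroup are descriptive.

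The cost is wording and one additional analysis on data the protocol already collects. The downside is a few more exclusions from the primary set: in the balanced illustration at 40% vs 65%, 54 becomes 48.6 per arm.

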#### Intervention description {11a}

Participants will be randomly allocated to their inclusion in one of two groups:Continuation of current immunosuppression regimen including mycophenolate, available in the form of mycophenolate sodium or mycophenolate mofetilCessation of mycophenolate, and commencement of rapamycin, available as sirolimus (Rapamune®, Pfizer Australia Pty Ltd)

The study products will be provided through the patients’ elected pharmacy. Control arm participants will continue their usual immunosuppression regimen as directed by their treating nephrologist, with standard target trough tacrolimus levels in our institutions ranging from 5 to 8 ng/mL [29]. Intervention arm participants will cease mycophenolate the day prior to commencing sirolimus 2mg daily. Trough drug levels will be taken at days 5–7 with dose titration targeting trough level 6 ng/mL and ongoing weekly levels to ensure stabilisation prior to vaccination.

All trial participants will receive a third “booster” dose of a COVID-19 mRNA vaccine, either Pfizer-BioNTech BNT162b2 (30 μg, IM) or Moderna mRNA-1273 (50 μg, IM) determined by local practice and vaccine availability. Study participants will receive written pre-vaccination information on the benefits and potential risks and harms of the COVID-19 vaccine and be screened for contraindications to immunisation such as serious adverse events attributable to a previous dose of a mRNA COVID-19 vaccine. All patients will be advised of the need to continue with additional public health measures (i.e. physical distancing, hand washing, wearing a face mask, and COVID-19 testing and isolation as required).

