#### Criteria for discontinuing or modifying allocated interventions {11b}

Sirolimus has known dose-related adverse effects (AEs). Trough level targets of 6 ng/mL are generally well tolerated [30]. Participants who experience severe adverse events will cease sirolimus and return to their usual immunosuppression regimen. Participants who experience mild AEs related to sirolimus trough levels above target will have their dose reduced. Participants who continue to experience mild AEs (mouth ulcers, peripheral oedema) at target trough level will be offered the option of discontinuing the study intervention and continuing with trial follow-up.

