#### Strategies to improve adherence to interventions {11c}

RIVASTIM-rapamycin uses the combination of tacrolimus and sirolimus to facilitate lower target sirolimus and tacrolimus exposure without an increase in the risk of graft rejection [28]. This reduces the likelihood of sirolimus-associated adverse events which are generally dose-related. Following randomisation, participants in the intervention arm will have weekly blood tests for dose titration and to ensure adequate adherence.

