### Relevant concomitant care permitted or prohibited during the trial {11d}

All participants will continue with usual transplant management as per local standard of care and at the discretion of their treating nephrologist. Any changes to medications will be recorded. Participants will be asked to continue with their usual diet and medications.

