### Methods in analysis to handle protocol non-adherence and any statistical methods to handle missing data {20c}

A per-protocol analysis will also be reported, with participants who failed to adhere or tolerate sirolimus, and participants who withdrew or were lost to follow-up excluded from the analysis. Multiple imputation will be used to handle data missing at random from baseline characteristics. Data missing at random for the primary and secondary outcome will not be imputed, with these cases excluded from ITT analysis. If > 10% of the primary outcome data is determined to be missing not at random, a best-worst and worst-best case sensitivity analyses will be performed.

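### The per-protocol exclusion for non-adherence or intolerance applies to sirolimus only, so the comparison is asymmetric and open to selection bias of uncertain direction and size

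*Protocol article*

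**What the plan says.** The section on statistical methods for primary and secondary outcomes {20a} makes intention-to-treat primary: "The primary analysis will be by intention-to-treat, with participants assessed according to their treatment allocation". It then adds a per-protocol analysis, "with participants who failed to adhere or tolerate sirolimus, and participants who withdrew or were lost to follow-up excluded from the analysis". The section on non-adherence and missing data {20c} repeats the rule, again naming "participants who failed to adhere or tolerate sirolimus", and adds no criterion for mycophenolate.

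Other sections bear on who the rule can reach:

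- **Control regimen.** Intervention description {11a}: "Control arm participants will continue their usual immunosuppression regimen as directed by their treating nephrologist", with mycophenolate named as part of it. Trial design {8} has both groups stay on their assigned immunosuppression at least until the antibody measurement.
- **Room for change.** Concomitant care {11d}: "All participants will continue with usual transplant management as per local standard of care and at the discretion of their treating nephrologist". The same section says that medication changes are recorded.
- **Adherence checks.** Section {11c}: "participants in the intervention arm will have weekly blood tests for dose titration and to ensure adequate adherence". No counterpart is described for controls.
- **Stopping sirolimus.** Section {11b}: "Participants who experience severe adverse events will cease sirolimus and return to their usual immunosuppression regimen". Those with persisting mild effects at the target level may also stop and remain in follow-up.

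**The concern.** A per-protocol set is meant to compare the two regimens as assigned. Here the regimens are a switch to sirolimus and continued mycophenolate, so each arm has something to depart from. The written rule recognises departure in one arm only. A control who came off mycophenolate is off the allocated regimen by the protocol's own description, yet is kept.

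This has two consequences. First, the sirolimus arm is cut down to those who tolerated and took a new drug, and no matching group is identified in control, so randomisation no longer balances the two sides. Second, the control arm still contains any off-regimen participants. The result estimates neither the effect of allocation nor the effect of following the allocated regimens.

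At stake is how the per-protocol result is read. If it differs from the intention-to-treat result, a reader cannot tell whether adherence or selection explains the gap. The adherence and tolerance rule is probably the main difference between the two sets, because {20c} already drops outcomes missing at random from the intention-to-treat analysis.

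**Working it through.** The plan gives no figure for the size of the per-protocol set or for response in those excluded, so there is nothing to reproduce. The check has a textual part and an illustrative part.

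**Who can be excluded**

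| Reason | Sirolimus arm | Control arm |
|---|---|---|
| Withdrew or lost to follow-up | excluded | excluded |
| Did not adhere to or tolerate sirolimus | excluded | cannot apply |
| Stopped, reduced or did not take mycophenolate | not applicable (ceased by design) | kept |

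**Size of the shift when there is no effect**

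Inputs, all assumed because the documents give none:

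- p = response proportion over the whole of each arm as randomised, equal in both (40–60% tried)
- q = fraction of the sirolimus arm excluded (10%, 20%, 30%)
- d = response in retained minus response in excluded sirolimus participants (+20, 0, −20 points)

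Let r be response in the retained. Then p = (1 − q)·r + q·(r − d), so r = p + q·d. The control arm stays at p, so the spurious per-protocol difference is **r − p = q·d**, whatever p is.

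Example: p = 50%, q = 20%, d = 20 points. Retained respond at 54% and excluded at 34%; check 0.8 × 54 + 0.2 × 34 = 50. The shift is 0.20 × 20 = +4 points.

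| Excluded (q) | d = +20 | d = 0 | d = −20 |
|---|---|---|---|
| 10% | +2 | 0 | −2 |
| 20% | +4 | 0 | −4 |
| 30% | +6 | 0 | −6 |

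**Effect on a 5% two-sided test**

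This uses a normal approximation with 54 evaluable per arm before exclusion (60 planned × 0.9 for the stated 10% drop-out). Recruitment closed early, so 54 is illustrative. For the example, n is 54 in control and 54 × 0.8 = 43.2 in sirolimus. The pooled proportion is (27 + 23.328)/97.2 = 0.518, the null standard error is 0.1020 and the actual standard error is 0.1019. The rejection probability is P(Z > (1.96 × 0.1020 − 0.04)/0.1019) + P(Z < (−1.96 × 0.1020 − 0.04)/0.1019) = 0.0582 + 0.0093, about 0.068. Over p = 40–60%, the values are about 0.055, 0.068 and 0.087–0.089 for q = 10%, 20% and 30% when d is 20 points in either direction, and 0.050 when d = 0.

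**Would a symmetric rule remove the shift?**

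Let the control arm also lose a fraction q_c with gap d_c, defined in the same way. The difference becomes q·d − q_c·d_c. With q = 20%, d = +20 and q_c = 10%:

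- d_c = +20: 4 − 2 = +2 points
- d_c = −20 (excluded controls respond better): 4 + 2 = +6 points

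The second case fits the premise under choice of comparators {6b}, that mycophenolate is associated with a suppressed antibody response. A symmetric rule makes the estimand coherent but does not in itself remove the selection.

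**The case against.** The strongest reply has four parts.

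1. *Intention-to-treat is primary and the per-protocol analysis is additional.* This stands. The primary test and conclusion do not depend on the rule.
2. *The rule names sirolimus because only that arm starts a new drug; controls enter already taking mycophenolate.* This explains the wording, and control departures may be few. It does not make the rule symmetric: control treatment is left to the nephrologist, and both arms are meant to stay on their regimen until sampling.
3. *Controls are not wholly unselected.* Correct. Withdrawals and losses leave both arms; the controls are unselected only on adherence and tolerance.
4. *Details of a per-protocol set belong in the analysis plan.* That holds for adherence thresholds and sampling windows, and their absence here is not criticised. The exclusion rule itself, however, is written out twice, in one-sided form.

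A reader might infer that the analysis is biased in favour of sirolimus. That would follow if intolerant participants were frailer and poorer vaccine responders, which is plausible, but the documents do not say how such participants respond. They also leave room for the opposite sign. On the premise in {6b}, controls who stopped mycophenolate and were kept would raise the control rate and push against sirolimus. Sections {11b} and {11c} describe sirolimus adverse effects as dose-related, so intolerant participants may be the more highly exposed rather than the weaker responders.

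**Conclusion.** The concern holds as one of asymmetry. The adherence and tolerance exclusion, as stated in {20a} and {20c}, acts on the sirolimus arm only, and the resulting comparison is open to selection bias whose direction and size the documents do not fix. Under the assumed rates above, the shift with no true effect lies anywhere from −6 to +6 points, and is zero if excluded and retained participants respond alike. For scale, the trial is designed to detect a 25-point difference. The illustration rests on assumed exclusion fractions of 10–30% and an assumed gap of 20 points; other values scale as q × d. The stronger conclusion, that the bias favours sirolimus, is not supported. The point affects a secondary analysis and is worth correcting, but does not touch the primary result.

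**What to change.** Define the per-protocol set by one rule for both arms: third vaccine dose received, and allocated regimen continued from randomisation to the primary blood sample, meaning mycophenolate in control and sirolimus in intervention. Apply it using the medication changes that {11d} says are recorded for all participants. Report exclusions by arm and reason.

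Because this rule still selects on behaviour after randomisation, base any statement about the effect in adherers on a complier-average (instrumental-variable) or inverse-probability-weighted estimate, with its assumptions stated. The first assumes that allocation does not affect outcome in those whose treatment it does not change, which is questionable for people who took sirolimus for a time and then stopped. The second needs recorded predictors of adherence and will be imprecise at this sample size. Section {18b} asks those who discontinue to remain in follow-up, so many of their outcomes should be available. Describe the per-protocol result as supportive of the intention-to-treat analysis.

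The cost is a wording change in {20a}, {20c} and the analysis plan, a few controls lost from the per-protocol set, and a little more analysis work. Weekly adherence tests are described only for the intervention arm, so missed doses in control may be less completely captured; this should be stated as a limitation.
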